### The secondary outcomes

#### Clinical outcomes

Information on biochemical markers as eGFR, creatinine, albumin, haemoglobin and creatinine will be obtained from the electronic health record. Data on hospitalisation and admission days, transplantation and end-stage renal disease and mortality are obtained from The Hospital Business Intelligence Register in Central Denmark Region.

#### Resource Utilisation

Number of contacts includes all contacts to the outpatient clinic in the follow-up period, including face-to-face consultations, telephone consultations and additional contacts in the outpatient clinic. In addition, other hospital care contacts and hospitalisations will be obtained from the Hospital Business Intelligence Register in Central Denmark Region. Additional information on the nature of resource utilisation will be obtained and captured in REDCAP (Research Electronic Data Capture). REDCap is a secure, web-based application designed to support data capture for research studies [35].

#### Patient-reported outcomes

Quality of life (QOL) will be measured by EuroQol EQ-5D-5 L [36]. The EQ-5D-5 L questionnaire measures individual generic health status using five dimensions: mobility, self-care, usual activities, pain/discomfort, and anxiety/depression, and each dimension has five levels depending on severity of symptoms (1 no problems, 5 extreme problems) and a visual analogue scale. The scores can then be converted into a single index number. The index value will be used for calculation of quality-adjusted life years for a health economic analysis of the intervention, which will be conducted after completion of this study. The EQ-5D scale is favoured for use in patients with chronic kidney disease due to ease of use for patients [37]. Illness perception will be measured by the IPQ-B (Brief Illness Perception Questionnaire), which comprises five components. Each of these components holds a perception about one aspect of the illness, and together they provide an individual’s coherent view of an illness [38]. The IPQ-B is widely used and has sound psychometric properties [39].Self-efficacy will be measured by using the Danish version of General Self-Efficacy Scale (GSE) [40, 41]. GSE was designed to assess optimistic self-belief to cope with difficult demands in life [40, 41]. GSE includes 10 items with a response range from 1 “not at all true” to 4 “exactly true”. The GSE scale has been used in a range of research projects in different countries and populations, where it typically yielded sufficient psychometric properties [42]. Confidence, safety and satisfaction will be measured by using ad hoc items developed from the Danish PREM (Patient-Reported Experience Measure) questionnaire from the Danish Cancer Society.

All outcomes will be compared in the three groups and measured at baseline and after 6, 12 and 18 months of follow-up or at the time a patient leaves the study due to patient wish, death, transplantation or initiation of dialyses.

### Demographic, clinical and laboratory variables

Demographic factors such as gender, age, education and current employment status will be obtained from the introductory questionnaire. Clinical factors like comorbidity due to malignancy, diabetes mellitus, chronic obstructive airways disease, cerebrovascular disease, ischaemic heart disease and peripheral vascular disease are categorised according to the Charlson Comorbidity Index [43]. Biochemistry results from the clinical laboratory will be obtained from tests performed in accordance with the current standard of care.

### Other measurements

Prior to entering the study, an introduction PRO questionnaire (iPad or in paper form) will be handed out to all eligible patients to investigate whether patients participating in this study have higher health literacy skills and self-efficacy than those who decline to take part in the study or wish to drop out. Nutbeam defines HL as *“The personal, cognitive and social skills which determine the ability of individuals to gain access to, understand, and use information to promote and maintain good health*” [44]. Health literacy will be measured by using the Danish version of Health Literacy Questionnaire (HLQ) [45, 46]. The HLQ includes nine conceptually subscales with a total of 44 items. The HLQ has well-documented psychometric properties [46]. In this study, the HLQ subscales 4 (Social support for health), 6 (Ability to actively engage with healthcare providers) and 9 (Understand health information well enough to know what to do) will be used. Patient activation will be measured by two modified items from the Danish version of the Patient Activation Measures (PAM) [47]. During the analysis phase, we intend to use this data to evaluate our hypothesis that patients choosing to participate in this study may have higher health literacy skills and self-efficacy than those who decline to take part or who drop out.

### Statistical methods

The three randomisation groups will be compared in intention-to-treat analysis and per protocol as recommended in non-inferiority trials [48]. The primary comparison groups will be composed of those receiving usual care, versus each of the intervention groups separately. Analysis methods will be chosen according to the data type of the outcome under investigation.
*Continuous endpoints (*e.g. *quality of life, estimated Glomerular Filtration Rate)*: These data will be summarised using means and standard deviations, with differences in means and 95% confidence intervals reported. Longitudinal plots of the data over time will also be constructed for visual presentation of the data. The primary analysis will be adjusted for covariates identified as potentially prognostic variables (e.g. sex and age) in a multiple linear regression model. A secondary unadjusted analysis will also be performed if covariate adjustment is not practical (e.g. due to low event rates).*Categorical (dichotomous) endpoints (*e.g. *PRO data, hospitalisation rates)*: For dichotomous secondary endpoints, the proportion of participants and percentages will be summarised between arms. Logistic regression will be used to produce estimates of relative risks and 95% confidence intervals.*Time-to-event endpoints (*e.g. *time to initiation of dialysis, mortality):* These endpoints will be modelled for each randomisation arm using survival analysis methods. Kaplan–Meier survival curves will be constructed for visual presentation of time-to-event comparisons. The primary analysis will be carried out using a Cox proportional hazards or an extended Cox model to include prognostic covariates. Hazard ratios will be produced with 95% confidence intervals.

Sensitivity analyses will be performed to test the robustness of the results in the presence of differences in the groups.

Sample size was estimated for the primary outcome loss of renal function (eGFR). From literature review, the non-inferiority limit for eGFR is determined to be 2.85 mL/min/1.73 m^2^/year [49]. Based on a literature review, the assumptions are an approximate loss in eGFR of 5 mL/min/1.73 m^2^/year, SD: 4 mL/min/1.73 [49]. Loss in eGFR is normally distributed. Given 80% statistical power and *p*-value of 0.05, we need 50 patients in each group, in total 150 patients. With an estimate of 250 incident patients seen yearly, 150 patients will be reached in an inclusion period of 1 year and 2 months due to the expected attrition [50].

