### Study timeline

Inclusion and randomisation started in January 2019. Inclusion is expected to terminate in April 2020. Follow-up assessment will take place 6, 12 and 18 months after randomisation. Figure 2 presents the flowchart on inclusion of the participants. Baseline and follow-up PRO assessments are shown in Table 1.

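### Logistic regression is paired with relative risks without a step that yields them, and hospitalisation rates are classed as dichotomous without follow-up time

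*Protocol article*

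**What the plan says.** The Statistical methods section of the Protocol article sorts endpoints into continuous, dichotomous and time-to-event classes. The examples given for the dichotomous class are "PRO data, hospitalisation rates". The descriptive rule for this class is: "For dichotomous secondary endpoints, the proportion of participants and percentages will be summarised between arms". The model rule is: "Logistic regression will be used to produce estimates of relative risks and 95% confidence intervals".

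The time-to-event class, analysed by Cox regression with hazard ratios, has as its examples "time to initiation of dialysis, mortality". Hospitalisation is not named there, and no class is described for counts or rates.

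On follow-up, the Study timeline says: "Follow-up assessment will take place 6, 12 and 18 months after randomisation". The section on patient-reported outcomes adds that outcomes are measured at those times or "at the time a patient leaves the study due to patient wish, death, transplantation or initiation of dialyses". On the source of the data, the section on secondary clinical outcomes says: "Data on hospitalisation and admission days, transplantation and end-stage renal disease and mortality are obtained from The Hospital Business Intelligence Register".

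**The concern.** Two things in the dichotomous paragraph do not fit together.

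- **Model and effect measure.** Exponentiating a logistic coefficient gives an odds ratio. A relative risk needs a different model or an extra step, and none is named. The other two classes pair model and measure correctly: linear regression with mean differences, Cox regression with hazard ratios. An analyst who follows the dichotomous rule literally could put a relative-risk label on an odds ratio. The odds ratio lies further from 1 than the relative risk, so a benefit or a harm would look larger than it is.

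- **Endpoint and class.** A rate has person-time in its denominator; a proportion of participants does not. Because patients may leave before 18 months, two patients with the same risk of admission per unit time can have different chances of being counted as admitted.

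Hospitalisation is a named secondary clinical outcome and bears on whether visits can safely be replaced. A mislabelled or exposure-dependent estimate would therefore matter to readers, even though it is not the primary outcome.

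**Working it through.** The article states no event risk, odds ratio or relative risk for any dichotomous endpoint, so there is no figure of its own to reproduce. The event risks, admission rates and mean follow-up times below are assumptions, chosen to show a range. The planned 18 months (1.5 years) is from the article.

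**1. Odds ratio read as a relative risk.** With control risk p and true relative risk RR, the intervention risk is RR × p, so

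OR = RR(1 − p) / (1 − RR × p).

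At p = 0.30 and RR = 1.5: 1.5 × 0.70 / (1 − 0.45) = 1.05 / 0.55 = 1.91.

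| Assumed control risk | OR when true RR is 1.5 | OR when true RR is 0.67 |
|---|---|---|
| 5% | 1.54 | 0.66 |
| 10% | 1.59 | 0.65 |
| 20% | 1.71 | 0.62 |
| 30% | 1.91 | 0.59 |
| 40% | 2.25 | 0.55 |

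At 5% a true 33% reduction would read as 34%, which is negligible. At 30% it would read as 41%, and a true 50% increase would read as 91%.

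**2. Can a logistic model yield a relative risk?** Yes, with one more step. In a simulated data set of 200,000 patients with control risk near 30% and one prognostic covariate, the fitted odds ratio was 0.60. Averaging the predicted risks with everyone set to each arm in turn, and taking their ratio, gave 0.70. The crude relative risk was also 0.70. The stated pairing is therefore achievable, but only through a step that the article does not name.

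**3. Follow-up time.** Assume the same constant admission rate λ in both arms and mean follow-up t. The proportion with any admission is 1 − exp(−λt).

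- λ = 0.4 per year, t = 1.5 years: 1 − exp(−0.60) = 45.1%.
- λ = 0.4 per year, t = 1.2 years: 1 − exp(−0.48) = 38.1%.
- Apparent RR = 38.1 / 45.1 = 0.85 (0.845 before rounding); apparent OR = (0.381/0.619) / (0.451/0.549) = 0.75. There is no true difference.

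With λ = 0.2 per year the same contrast gives RR 0.82 and OR 0.78. With λ = 0.6 per year it gives RR 0.87 and OR 0.72. With t = 1.5 years in both arms all these ratios are 1.00. The distortion therefore needs follow-up to differ between arms.

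**The case against.** The strongest reply is that the sentence sets an aim, to produce relative risks, and does not say that exponentiated coefficients will be given that label. Logistic regression can serve that aim through standardisation, and an analysis plan that is not shown may say so. This stands as a limit on the consequence: a reader might infer that effects will be reported in exaggerated form, and the document does not establish that. It does not remove the mismatch, because the sentence as written names a model and a measure that the model does not directly give.

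A reader might also assume that hospitalisation is common in this population, which would make the error large. The article gives no hospitalisation risk, and its exclusion criteria remove several high-risk groups. The article does mention low event rates, but in the continuous-endpoint paragraph, so it does not show that admissions are rare either. The size is unknown, and the range in the table is the honest statement of it. Arm-level proportions will also be reported, so a crude relative risk could be checked by hand.

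On hospitalisation, the proportion with any admission is a legitimate endpoint. The lists are examples, and the section says methods will follow the data type. A reader might infer that repeat admissions and admission days will be discarded, or that a negative binomial model is required. Neither follows: the article does not say that those counts will be reduced to yes/no, and a count model is one option among several.

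Finally, no differential exit is documented, and register data need not stop when questionnaires do. That is correct, and it makes the bias conditional. Against this, the trial is unblinded, the Discussion names loss to follow-up as a main concern, and it suggests patients may prefer seeing a physician at the hospital. Exit that differs by arm is thus plausible, but not shown.

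**Conclusion.** The point holds in a limited form. The article states a model and an effect measure that do not match without a further step, and it names no such step.

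The harm arises only if odds ratios are labelled relative risks, and its size depends on event risks that the documents do not give. A true relative risk of 1.5 would read as 1.54 at an assumed control risk of 5% and as 2.25 at 40%.

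Separately, classing hospitalisation rates as dichotomous leaves follow-up time out, although early exit is foreseen. Under assumed equal rates of 0.4 per year and mean follow-up of 1.2 against 1.5 years, this would produce an apparent relative risk of 0.85 from no true difference. With equal follow-up it would produce no bias.

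Only secondary endpoints are affected. The non-inferiority conclusion on eGFR does not depend on either issue.

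**What to change.** In the analysis plan, replace the sentence on logistic regression with one of two choices:

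- estimate relative risks with 95% confidence intervals by modified Poisson regression with robust standard errors, by log-binomial regression, or by marginal standardisation from the logistic model, naming the one used; or
- keep logistic regression and report its results as odds ratios.

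Then define the hospitalisation endpoint in one sentence, as any of:

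- any admission by a fixed time, stating how patients who leave before that time are handled;
- time to first admission; or
- number of admissions, modelled as a count with a log follow-up-time offset and reported as a rate ratio.

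The hospitalisation data are already to be obtained from the register. The cost is about two sentences, settled before the arms are compared, with no new data collection and no change to the sample size.

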## Discussion

The use of PROs in clinical practice has become increasingly common during recent years [51]. However, there is limited scientific evidence to guide clinical practice and only few international experiences to draw on. PROs often compose a supplement to the patient’s follow-up, but are infrequently used as the basis for outpatient follow-up. The focus of this trial will be to evaluate whether PRO-based follow-up is at least as effective as usual outpatient follow-up in managing decline in renal function and maintaining patients’ quality of life. Furthermore, we intend to identify the target patient group for using PRO-based follow-up, since we believe that not all patients will benefit from PRO-based follow-up. The results may help identifying patient groups that are suitable for PRO-based follow-up and thereby promote future PRO implementation.

The nephrology outpatient clinics at Aarhus University Hospital and Regional Hospital Central Jutland, Viborg have used PRO as a complimentary tool for consultations the last few years [52], and are therefore familiar with the clinical use of PRO. This could be an advantage regarding the understanding of the software and understanding the PRO overview in the electronic health record. On the other hand, it could disturb the intervention if the clinicians use PROs as a part of daily practice alongside this study. This has been taken into consideration during the initiation of this study. Ideally, all use of PROs in daily clinical practice should be limited during this study period; however, this would not be acceptable for the patients in the nephrology outpatient clinics since it is a part of their usual follow-up. Another concern is the willingness of the patients to participate in this study due to the 3-arm design. The study population consists mostly of fragile elderly patients whose preferences may be to attend regular follow-up at the hospital facing a physician. In the pilot phase, an assessment of the sample size will be done. Loss to follow-up is one of the main concerns in randomised controlled studies [53]. Loss of statistical efficiency can be overcome by increasing the number of participants in the study [54]. If a lower participation rate than expected occurs, we will consider: (i) opening up recruitment to patients already attending the clinic (i.e. those currently in follow-up); and (ii) inviting other nephrology centres to participate in the study.

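### Kaplan-Meier curves for time to dialysis will modestly overstate the risk of starting dialysis, because death and transplantation end follow-up; cumulative incidence curves should replace them

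*Protocol article*

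**What the plan says.** The Statistical methods section of the protocol article gives "time to initiation of dialysis, mortality" as examples of time-to-event endpoints. For these, Kaplan-Meier "survival curves will be constructed for visual presentation of time-to-event comparisons". The inferential method is also named: "The primary analysis will be carried out using a Cox proportional hazards or an extended Cox model to include prognostic covariates", with hazard ratios and 95% confidence intervals. In that sentence the primary analysis means the main analysis of these secondary endpoints. The trial's primary outcome is change in eGFR.

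The last paragraph under Patient-reported outcomes, which is worded to cover all outcomes, sets measurement at the scheduled times or "at the time a patient leaves the study due to patient wish, death, transplantation or initiation of dialyses". The Study timeline fixes the horizon: "Follow-up assessment will take place 6, 12 and 18 months after randomisation".

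Table 2 lists mortality, initiation of dialysis and transplantation on separate lines. The Clinical outcomes section confirms that all are captured: "Data on hospitalisation and admission days, transplantation and end-stage renal disease and mortality are obtained from" a regional hospital register. The article mentions no cumulative incidence function, competing-risk method or combined kidney-failure endpoint. It also states no censoring rule for patients who die or are transplanted before dialysis.

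**The concern.** A patient who dies can no longer start dialysis. A patient transplanted before dialysis leaves observation without the event. Kaplan-Meier has one way to handle either exit, which is to censor it. Censoring treats the patient as someone who would have gone on to face the same dialysis risk as those still under observation. One minus Kaplan-Meier then describes a hypothetical population in which nobody dies or is transplanted, and as an absolute risk for the enrolled patients it is too high.

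Deaths are foreseeable here, since the Discussion says: "The study population consists mostly of fragile elderly patients". Transplantation before dialysis raises a further question of interpretation. It is kidney failure treated in another way, yet on a dialysis-only curve it would look like an exit free of the event.

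What is at stake is how a secondary safety-type outcome is read in a trial that replaces visits with questionnaires. A reader who takes the curve's height as the probability of dialysis will take too large a figure, and the excess will be larger in an arm with more deaths or transplants.

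**Working it through.** **Plan's own figure.** There is none to reproduce. The article gives no rate, event count or power for dialysis, death or transplantation, so every rate below is an assumption.

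**Inputs from the article.** Follow-up is T = 1.5 years (Study timeline). The arm size is 50: "Given 80% statistical power and *p*-value of 0.05, we need 50 patients in each group, in total 150 patients".

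**Formulas, with constant hazards.** Let d be the annual hazard of dialysis and c the annual hazard of death or transplantation before dialysis.
- With competing exits censored: 1 − KM = 1 − exp(−d·T)
- Actual proportion starting dialysis: CIF = d/(d + c) × [1 − exp(−(d + c)·T)]

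**Step 1: assumed hazards, d from 0.03 to 0.10 and c from 0.03 to 0.20.** Selected rows:

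| d | c | 1 − KM | CIF | Excess, points | Expected starts per 50: KM vs CIF |
|---|---|---|---|---|---|
| 0.03 | 0.03 | 4.40% | 4.30% | 0.10 | 2.20 vs 2.15 |
| 0.05 | 0.05 | 7.23% | 6.96% | 0.26 | 3.61 vs 3.48 |
| 0.05 | 0.10 | 7.23% | 6.72% | 0.51 | 3.61 vs 3.36 |
| 0.10 | 0.10 | 13.93% | 12.96% | 0.97 | 6.96 vs 6.48 |
| 0.10 | 0.20 | 13.93% | 12.08% | 1.85 | 6.96 vs 6.04 |

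Over the whole grid the excess is 0.1 to 1.9 points, 2% to 16% in relative terms, and less than one patient per arm.

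**Step 2: assumed 18-month risks, including higher ones.** Let p be the actual dialysis risk and q the risk of death or transplantation first. The total cumulative hazard is −ln(1 − p − q), and the dialysis share is p/(p + q).
- p = 10%, q = 10%: 0.2231 × 0.5 = 0.1116, so 1 − KM = 10.6%. Excess 0.6 points.
- p = 15%, q = 20%: 0.4308 × 15/35 = 0.1846, so 1 − KM = 16.9%. Excess 1.9 points.
- p = 20%, q = 20%: 0.5108 × 0.5 = 0.2554, so 1 − KM = 22.5%. Excess 2.5 points.

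Multiplied by 50, these excesses are 0.3, 0.9 and 1.3 patients per arm. Steps 1 and 2 together give the range of 0.1 to 2.5 points.

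**Step 3: arms with different competing hazards.** Take d = 0.10 in both arms, with c = 0.05 in one and 0.15 in the other. Both Kaplan-Meier curves reach 13.9%. The cumulative incidences are (0.10/0.15) × [1 − exp(−0.225)] = 13.4% and (0.10/0.25) × [1 − exp(−0.375)] = 12.5%, a ratio of 0.93. The Kaplan-Meier excess is therefore 0.5 points in one arm and 1.4 in the other. The dialysis hazards are equal by construction, so the cause-specific hazard ratio is 1. A Cox model that censors competing exits estimates exactly that quantity.

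**Step 4: what counts as the renal event.** With deaths ignored and d = 0.05, dialysis alone gives 1 − exp(−0.075) = 7.2%. Counting transplantation as well, at an assumed annual hazard of 0.01 or 0.03, gives 1 − exp(−0.09) = 8.6% or 1 − exp(−0.12) = 11.3%. This gap reflects two different event definitions, not a bias in either estimate.

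**The case against.** The strongest reply has four parts.

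*The censoring rule is not written down.* The sentence on leaving the study says when outcomes are measured. It defines neither events nor censoring, and a condensed article can leave both to an analysis plan. This stands in part. A reader might infer that the protocol scores a pre-emptive transplant as a success, but no section says so, and transplantation has its own line in Table 2 and so is not hidden. The article does name the curve, however, and that curve can only censor.

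*The inference is sound.* This stands in full. A reader might conclude that the Cox analysis is biased or invalid. It is not: with competing exits censored it validly estimates the cause-specific hazard ratio. The criticism concerns curves shown for visual presentation of a secondary outcome.

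*Cumulative incidence can mislead too.* In Step 3 the arm with more competing exits shows less dialysis on the cumulative incidence scale although the hazards are equal. This is correct, and it is why those curves must be read beside mortality. It does not make 1 minus Kaplan-Meier an absolute risk.

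*The effect is small.* The exclusion criteria remove patients with a received or scheduled transplant, projected end-stage disease within 12 months, or expected death within 6 months. Referral is typically at an eGFR of about 30 to 40, and the assumed loss is 5 per year, or 7.5 over 18 months. A typical patient therefore ends near 22.5 to 32.5, although inclusion reaches down to 10. This stands and limits the weight of the point. It also means that frailty cannot be used to argue for both many deaths and many transplants.

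A composite with death would gain events, but wide intervals on rare secondary outcomes are expected in a trial sized for eGFR. The lack of such a composite is not an error.

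**Conclusion.** The concern holds in a limited form. The article assigns Kaplan-Meier to time to dialysis, lets death and transplantation end follow-up, and names no competing-event method. On the natural reading these exits are censored, and 1 minus Kaplan-Meier then overstates the absolute risk of starting dialysis whenever any such exit occurs.

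The size rests on assumed rates with constant hazards over 18 months: about 0.1 to 2.5 percentage points, or roughly one patient or fewer per arm of 50. The upper end needs 20% dialysis and 20% death or transplantation, for which the article offers no support.

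The documents do not support a claim of large or serious distortion, of an invalid hazard ratio, or of a dialysis endpoint that has to be redefined. This is an inexpensive improvement in presentation and labelling. It does not affect the eGFR comparison.

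**What to change.** In the time-to-event item of Statistical methods:
- Replace the Kaplan-Meier curve for dialysis with Aalen-Johansen cumulative incidence curves by arm. Treat death and transplantation before dialysis as competing events, and show the curves beside the mortality curve.
- Keep the Cox model for dialysis and label its result a cause-specific hazard ratio.
- Add a supportive analysis that counts dialysis or transplantation together as kidney failure, with death competing, so that a transplant before dialysis is not read as a dialysis-free outcome.
- A composite of kidney failure or death is optional.
- Keep Kaplan-Meier for mortality, and state that deaths after dialysis or transplantation are still counted. Read literally, the rule on leaving the study would stop this, although the register can supply these deaths.

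The cost is a few sentences of plan text and a few lines of code. Dialysis, transplantation and death are already obtained from the health record or register. The downside is one additional curve and one supportive analysis to report. The wording should be settled before outcomes are compared by arm.

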### Hypothesis

#### Three a priori hypotheses will be tested

Non-inferiority will be reached for both patients in the PRO-based remote follow-up and the PRO-based telephone consultations for the primary endpoint, loss of renal function (eGFR).Patients in the PRO-based remote follow-up and the PRO-based telephone consultations will perceive less deterioration in quality of life, but increased satisfaction and a gain a deeper understanding of illness perception than patients in usual care.Use of healthcare resources is less in the PRO-based remote follow-up and the PRO-based telephone consultations compared to usual follow-up

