### Design

The PROKID study is a non-inferiority pragmatic multi-centre three-arm randomised controlled trial of adults with advanced CKD [25]. Participants will be randomised in a ratio of 1:1:1 to receive one of the following: (a) PRO-based remote follow-up, (b) PRO-based telephone consultations or (c) Usual outpatient follow-up visits. The study follows the SPIRIT checklist: Standard protocol for clinical trials [26, 27].

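### The 50 patients per group is not reproduced by the margin, SD, power and alpha printed with it, so an input is misprinted or unstated

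*Protocol article*

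**What the plan says.** All inputs and the result stand together in the sample size paragraph under Statistical methods in the protocol article:

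- Margin: "the non-inferiority limit for eGFR is determined to be 2.85 mL/min/1.73 m^2^/year".
- Expected loss and spread: "an approximate loss in eGFR of 5 mL/min/1.73 m^2^/year, SD: 4 mL/min/1.73". The SD carries no time unit, although the loss does.
- Error rates: "Given 80% statistical power and *p*-value of 0.05". Sidedness is not given.
- Result: "we need 50 patients in each group, in total 150 patients".

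Two other places bear on the calculation. Continuous endpoints, eGFR among them, are to be analysed "with differences in means and 95% confidence intervals reported", which for non-inferiority corresponds to one-sided 0.025. Under Design, "Participants will be randomised in a ratio of 1:1:1", so the groups are equal in size. Each intervention arm is compared separately with usual care. The paragraph gives no assumed true difference, multiplicity adjustment or attrition rate. Attrition is mentioned only in explaining the 14-month inclusion period.

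**The concern.** The paragraph is written as a calculation: given these inputs, this number is needed. A reader who repeats it gets about three fifths of the printed number or less. That is too large a gap for rounding, or for the choice between a normal and a t-based formula.

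The number itself may be adequate. What is lost is knowledge of what it provides. If SD 4 is right and 50 means evaluable patients, the trial has a comfortable reserve. If the SD was really about 5, 50 is the bare minimum with nothing left for loss to follow-up. If 50 already includes an attrition allowance, the evaluable target is lower. The Discussion names loss to follow-up as a main concern and plans a sample size assessment in the pilot phase. That assessment needs to know which case applies.

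**Working it through.** **Inputs.** Margin Δ = 2.85 per year, SD σ = 4, power 80% and alpha 0.05, all from the sample size paragraph. Equal groups, from Design. True difference 0 is my assumption, as none is stated.

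**Formula.** n per group = 2(z₁₋α + z₁₋β)² σ² / Δ², with Δ² = 8.1225.

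**Attempt to reproduce 50.**

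- One-sided 0.025: 2 × 7.849 × 16 / 8.1225 = 30.9, so 31 per group (32 with the t distribution).
- One-sided 0.05: 2 × 6.183 × 16 / 8.1225 = 24.4, so 25 per group (26 with t).

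The printed 50 is not reproduced.

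**Power of 50 per group at SD 4.** The standardised margin is 2.85 / (4 × √(2/50)) = 2.85 / 0.8 = 3.56.

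- One-sided 0.025: Φ(3.56 − 1.96) = 94.5% (94.1% by noncentral t).
- One-sided 0.05: Φ(3.56 − 1.645) = 97.2% (97.1% by t).

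**Other standard variants, SD 4, per group (normal formula).**

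| Variant | n |
|---|---|
| Bonferroni for two comparisons (one-sided 0.0125), 80% power | 38 |
| One-sided 0.025, 90% power | 42 |
| Two one-sided tests for equivalence, 80% power | 34 to 42 |
| Margin and SD both scaled to 18 months | 31 |
| Margin scaled to 18 months, SD left at 4 | 14 |

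None gives 50 at the stated 80%. Raising the power does: 95% at one-sided 0.025 gives 52, and Bonferroni with 90% gives 49. Both abandon the printed 80%.

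**What would give about 50.**

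| Explanation | Arithmetic |
|---|---|
| SD 5 instead of 4 | 2 × 7.849 × 25 / 8.1225 = 48.3, so 49 (50 with t) |
| Unstated attrition, SD 4 | 1 − 32/50 = 36%; 1 − 31/50 = 38% |
| Bonferroni plus attrition, SD 4 | 1 − 38/50 = 24% |
| True difference of about 0.61 against the intervention, SD 4 | 2 × 7.849 × 16 / (2.85 − 0.61)² = 50.1 |
| Two-group total printed as a per-group number, one-sided 0.05 | 2 × 25 = 50 |

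The last four keep SD 4 and 80% power.

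**Power in the cases that matter** (one-sided 0.025; per comparison by noncentral t; both arms by the bivariate normal with correlation 0.5 from the shared control). The 40 per group is an illustrative 20% loss; the article gives no rate.

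| SD | Evaluable per group | Per comparison | Both arms |
|---|---|---|---|
| 4 | 50 | 94% | 90% |
| 4 | 40 | 88% | 82% |
| 5 | 50 | 81% | 70% |
| 5 | 40 | 71% | 58% |

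The SD at which 50 per group gives exactly 80% is 2.85 / (√(2/50) × 2.802) = 5.09 (normal formula, no dropout).

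**The case against.** The strongest reply is that the discrepancy is on the safe side. On the printed inputs 50 is more than enough, and at SD 4 even a 20% loss leaves 88% power per comparison. A condensed article may also leave the attrition rate to the full protocol, so 50 could be 31 to 32 inflated for dropout. The Discussion plans a sample size check in the pilot phase and names ways to widen recruitment.

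Most of this stands. It removes any claim that the trial is too small on its stated inputs, and the missing attrition rate is not a finding in itself. It does not rescue the sentence as printed, which presents 50 as the consequence of inputs that do not yield it.

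Three stronger readings are tempting, and the documents do not support them:

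- A reader might infer that either the SD or the power must be wrong. Attrition, multiplicity plus attrition, a non-zero assumed difference or a two-group total would each give about 50 with both intact.
- A reader might infer that the mean loss of 5 and the SD of 4 were swapped. SD 5 does give 50 by the t-based calculation, but it is one fit among several. Only the cited source could settle it.
- A reader might infer a power shortfall because the first hypothesis says that "Non-inferiority will be reached for both patients in the PRO-based remote follow-up and the PRO-based telephone consultations for the primary endpoint". The analysis compares usual care with each arm separately, and no rule requiring both to succeed is stated. Power for both arms is worth reporting, but it is secondary. At SD 4 it is about 90% with 50 evaluable per group.

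**Conclusion.** The sample size statement is wrong as written. The difference is 18 to 19 patients per group at one-sided 0.025 and 24 to 25 at one-sided 0.05. Put as power, it is about 94% or 97% against the stated 80%. This rests on a true difference of 0, equal groups, no multiplicity adjustment and an SD on the same yearly scale as the margin.

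Which input is at fault cannot be settled from the article. Power would be only about 80% before attrition if the real SD were about 5, and nothing in the article shows that it is. The point is a reporting error in a primary design figure that needs correction, not evidence of an underpowered trial.

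**What to change.** Check the SD, with its time unit, against the cited source, and print one set of inputs that yields the printed number, including sidedness and assumed true difference.

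- **If SD 4 stands**, choose one of two statements. Either 50 evaluable per group gives about 94% power per comparison (about 90% for both arms) at one-sided 0.025. Or 31 to 32 evaluable per group are needed, followed by the attrition, multiplicity adjustment or assumed difference that raises this to 50.
- **If the SD was really about 5**, correct it and state about 81% per comparison and about 70% for both arms with 50 evaluable per group, before attrition.
- **If 50 was a two-group total**, say so, and restate the power that 50 per group provides.

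The cost is one corrected paragraph and no extra patients. Only in the SD 5 case might the power picture become less favourable.
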